### Sample size

When patients receive treatment in groups, interactions between patients may lead to correlation of outcomes of patients in the same group [52] sometimes referred to as cluster. As with cluster randomised trials, sample size calculation needs to consider the possibility of intra-cluster correlation [53]. As there are no previous trials of group interventions for bipolar disorder that have considered clustering, we considered empirical evidence regarding the magnitude of clustering from cluster randomised trials. A previous trial [54] found a negligible clustering effect (0.0001) but this was from a small sample, and so would be imprecisely estimated. We have therefore assumed a small but not zero clustering effect equal to 0.05. Based on the outcomes from the two previous Barcelona protocol psychoeducation randomised controlled trials [7,8] a differential treatment effect of 0.22 was used (60% recurrence in the control group, 38% in the psychoeducation group). Power for 80% probability of detecting a difference at 0.05 level, 2-tailed testing requires 82 patients per arm. Assuming a mean group size of 18 and an intra-cluster correlation coefficient of 0.05, a design effect of 1.85 gives a sample size of 152 in each arm. We have assumed 15% loss to follow up [54] giving a total sample size of 179 per arm (358 in total). This is achieved by running 10 groups of 18 subjects in each arm (10 in the North West and 10 in the East Midlands) over 3 years. Initially 17-18 patents are recruited per group but with attrition there will be 13-14 patients per group, the ideal size for group psychoeducation based on 10 years experience [55].

### Economic evaluation

The relative costs and outcomes of the bipolar group psychoeducation are compared to those of the bipolar group support intervention. The perspective of the evaluation is that of health and social care agencies and patients, which are the key components of a societal perspective. The primary economic outcome measure is the incremental cost per quality adjusted life year (QALY) gained. Resource use data are collected using and economic patient questionnaire (EPQ) which includes questions from the Client Service Receipt Inventory [56] interview and service use questionnaires used in previous mental health trials. Quality adjusted life years will be estimated from the Euroqol (EQ-5D) [34] and published utility tariffs. The EQ-5D has been used successfully in previous trials of psychosis [57,58] and bipolar disorder [35]. The EPQ and Euroqol are completed at baseline, 32, 64 and 96 weeks follow-up. National unit costs are combined with service use data to estimate the direct costs of the interventions.

## Interventions

### Group Psychoeducation

The Bipolar Group Psychoeducation programme is run by three facilitators, two health professionals (usually one experienced and one in training), specially trained for the purpose, and one of a small group of mental health service users known as expert patients [59] trained for the purpose. The bipolar group psychoeducation programme in Barcelona used three therapists over the last 10 years given the large size of the groups [55]. The use of an expert patient in the role of therapist working with a health professional was not tried in Barcelona but was successfully piloted in Newcastle ([name], personal correspondence) before the start of the current trial. Feedback suggests the expert patient ensures the service user perspective is integral to the program and provides additional credibility to the programme in the eyes of the participants. The expert patient also serves as a role model for the participants in tasks such as life charting.

In accordance with the Barcelona protocol, the group psychoeducation programme has 21 sessions (see Table 2 for curriculum content of the programme). However, as recommended [55], the content has been brought up to date to reflect recent research evidence [3,5]. The content was adapted to expectations of English service users as stated by a panel of service users working with the trial. For example, the first session includes more content about the nature of bipolar disorder, a greater emphasis on the role of family and the carer, changes to the wording of the manual and handouts, and the English context of service provision. Embedded in this is the acquisition of specific skills by each individual including, life charting, recognition of early warning signs, problem solving and other forms of coping, sleep hygiene and care planning, as well as general skills of actively participating and working collaboratively in the groups.

**Table 2 T2:** Sessions of group psychoeducation treatment

Session number	Topic
1	Introduction to the group and defining bipolar disorder?
2	What causes and triggers bipolar disorder
3	Symptoms 1: mania and hypomania
4	Symptoms 2: depression and mixed episodes
5	Evolution of bipolar disorder and the future
6.	Treatment 1: mood stabilisers
7.	Treatment 2: antimanic drugs
8.	Treatment 3: antidepressants
9.	Pregnancy, genetic counselling and effects on families
10.	Prescribed drugs and alternative therapies
11.	Risks associated with treatment withdrawal
12.	Alcohol, smoking, diet and street drugs
13.	Early detection of mania and hypomania 1
14.	Early detection of mania and hypomania 2
15	Early detection of depression and mixed episodes 1
16	Early detection of depression and mixed episodes 2
17	What to do when a new phase is detected
18	Regularity of habits
19	Stress control techniques
20	Problem solving strategies
21	Finalisation of Stay Well Plan and Closure

The group sessions comprise a closed group ideally starting with 17 or 18 participants. In practice 25% of patients may not attend so the average group size is likely to be 12-14 participants. A manual has been produced with a handout given for each session covering the content of that session. The groups are run in a collaborative workshop with a brief didactic introduction of the topic for the session and the rest of the work taking the form of active interaction using the collective experience of the participants.

Any participant who misses a session will be provided printed materials for the session and an opportunity to discuss the materials before the next session. However, absence of five consecutive sessions is considered a drop-out from treatment and analysed as such when a "per protocol" analysis is performed of participants who adhered to the treatment protocol. Participants who miss occasional sessions are offered a complete set of handouts for these sessions. The work in the psychoeducation group builds on earlier sessions so the involvement of participants who had not attended earlier sessions might be disruptive to the other participants in the group without the opportunity to catch up. The same rules apply to the bipolar group support arm so that there is internal consistency within the RCT to maintain internal validity.

An aim of the bipolar group psychoeducation arm is for each participant to develop their own individualised relapse prevention programme (a "stay well plan"). This includes a list of people that it might be shared with including family members and clinicians, but the final decision on whether to share the care plan rests with the participant. The expert patient and health professionals taking the group are supervised by RM in the East Midlands and FL & SJ in the North West. In addition, the expert patients taking part in the groups can take part in a peer run supervisory group in the North West run by DM. The content and conduct of each session are recorded on written forms firstly by the therapists and then also by the participants (with the therapists not present) using the treatment fidelity checklist. The group sessions have not been audiotaped because if one or more participants did not agree then a session could not be taped.

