### Baseline and Outcome Measures

At baseline interview the Structured Clinical Interview for DSM-IV (SCID) is used to assess sociodemographic features, the presence of axis 1 comorbid psychopathology [23], the presence of borderline or antisocial personality disorder [24] and the number of previous bipolar episodes. Participants are also asked at baseline how effective they think each of the two treatments is likely to be and if they have any preference as to which group they are allocated to.

The primary outcome measure is:

• time to next bipolar episode, average weekly symptom score (both established using 16-weekly SCID Longitudinal Interval Follow-up Evaluation (LIFE) interviews [25,26] to generate weekly scores of mania and depression on 1-6 scale of severity), as we have previously used [20,21].

Secondary outcome measures include:

• time to next manic-type episode (mania, hypomania or mixed affective episode) and time to next depressive episode [20,21]

• assessment of mean and variability in weekly symptoms of mania type symptoms and depression symptoms using the LIFE [20,21]

• assessment of function using the Social Adjustment Scale [27] and SOFAS [28];

• observer and self-rated measures of mood: 17 item Hamilton-GRID (HDRS) [29,30]; Bech-Raphaelson Mania Scale (MAS) [31]; Hospital Anxiety & Depression Scale (HAD) [32];

• medication adherence (Medad) [33];

• health status and related utility values using the Euroqol 5D [34,35] and health and social care costs from a broadly societal perspective.

Further measures are used to explore the process of change with treatment:

• The Hayward Stigma Questionnaire [36], an eight-item self-report questionnaire to examine if effectiveness of the groups might be related to reductions in stigma.

• The KAB (Knowledge about Bipolar Disorder). This is based on the Knowledge About Schizophrenia Inventory [37], and asks questions on knowledge about bipolar disorder found in the group psychoeducation manual. The questions were tested on groups of service users with bipolar disorder before the trial to ensure that the questions were understood and that the KAB did not have either ceiling or floor effects. The questionnaire is used to determine if differences in outcome between the two groups might be due to differences in the knowledge of bipolar disorder acquired by the participants.

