• The Hypomania Interpretations Questionnaire [38], a 10-item self-report questionnaire to explore if either group changed positive self-dispositional appraisals for hypomania-related experiences.

• The Social Rhythm Metric [39,40] trait and diary forms are completed over one week. The habitual timing of 17 daily behaviours is assessed.providing information on the number, timing and frequency of occurrence of regular activities.

• The Short-Form 12 (SF-12) [41], a 12-item self-completed questionnaire evaluating eight domains of overall health (general health, role physical, physical function, bodily pain, vitality, social functioning, role emotional, and mental health) in the preceding four weeks summarised as physical component scores and mental component scores.

• The Early Warning Signs checklist [42], a 32-item and 31-item checklist of common early warning signs of depression and mania, and the timing of these signs in relation to the onset of a depressive or mania episode respectively.

• The Coping Strategies Checklist [20], a list of adaptive and maladaptive coping strategies employed with the onset of manic symptoms (40 items) [43] and depression (40 items) symptoms. The coping with depression checklist was derived from items from the Response Style Questionnaire [44], the Depression Coping Checklist [45], items from the coping with mania questionnaire [43] that were also relevant to depression according to a panel of service users from a UK service user organisation (the Bipolar Organisation: the Manic Depression Fellowship) plus four additional items suggested by these service users.

• The Brief Illness Perception Questionnaire [20,46], a 11-item self-report measure of beliefs about mood swings in bipolar disorder, each measure on a five point scale of strength of conviction.

In addition, weekly ratings of treatment fidelity for each treatment session during the 21 session treatment are taken using a short checklist designed specifically for this study. Participants are asked to provide feedback specifically on group cohesion [47] and group working alliance (WAI-S) [48] which are administered at weeks 3, 10 and 21 of follow-up.

Follow-up of each patient is for 96 weeks from randomisation. Patients who had not relapsed at 96 weeks are censored on the time to next bipolar episode outcome. SCID-LIFE interviews to collect time to next relapse are collected every 16 weeks alternating between telephone and face to face interview up to 96 weeks.

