### Analysis

Intention to treat using Kaplan-Meier recurrence-free curves with significance tests will be based on the Cox proportional hazards regression model. The level of dependence or heterogeneity among patterns of recurrence

within the same team was estimated by the intracluster correlation coefficient (ICC) using estimate of frailty from the shared frailty model [60]. Trial centre, and number of previous episodes of bipolar disorder, will be included as covariates. Analysis of quantitative secondary outcome measures will use linear mixed models including baseline covariates and random effects for therapy group [52]. The treatment effect may differ according to illness duration/number of episodes with a lesser treatment effect in patients with longer illness duration/more episodes based on findings of the MRC CBT trial [21]. This will be tested in a secondary analysis by adding a severity-treatment interaction into the above models.

The economic analysis will be adjusted for baseline covariates shown to be important predictors of future costs and outcomes (e.g. costs and service use prior to entry, health status and utility, clinical severity and duration of illness, socio-economic status). Bootstrap simulations will be used to estimate cost effectiveness acceptability, net benefit statistics and the likelihood that group psycho-education is cost effective compared to group support. Probabilistic simulation models will be used to explore the generalisability of the results to the UK.

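### The five-absence drop-out rule has no exemption for absence after a recurrence, so if drop-outs are excluded the per-protocol analysis can lose patients because they had the primary event

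*Protocol article*

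**What the plan says.** The rule stands in the protocol article under Group Psychoeducation: "absence of five consecutive sessions is considered a drop-out from treatment and analysed as such". The article ties it to a per-protocol analysis limited to adherent participants. It is extended to the comparator: "The same rules apply to the bipolar group support arm", on the ground that this keeps the trial internally valid. No other adherence criterion is given. The text does not mention the reason for absence or what happens to absences after a recurrence.

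The same section says "the group psychoeducation programme has 21 sessions", and the Design section makes them weekly. Under Baseline and Outcome Measures the primary outcome is listed as "time to next bipolar episode, average weekly symptom score", and "Follow-up of each patient is for 96 weeks from randomisation". Episodes that occur while the groups are running are therefore primary events.

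The Analysis section names the main approach: "Intention to treat using Kaplan-Meier recurrence-free curves with significance tests will be based on the Cox proportional hazards regression model". The per-protocol analysis is not mentioned there. It appears only in the description of the intervention.

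**The concern.** A per-protocol set should be determined by how treatment was taken up. Here membership can be determined by the outcome. The definition of recurrence that the article uses for patients lost to direct follow-up includes substantial loss of function, urgent care and hospital admission. Such events could plausibly keep someone away from a weekly group for five weeks. If that person is then excluded as a drop-out, the event goes too, and the remaining set is enriched for people who stayed well.

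Applying one rule to both arms does not cure this. Attendance is observed after randomisation, and the two formats may differ in how readily a relapsed participant keeps coming.

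A lesser issue is that a run of absences is a weak measure of exposure. Someone who attends rarely but regularly is not a drop-out, while someone who attends most sessions with one long gap is. The article says that later psychoeducation sessions build on earlier ones, and its Discussion looks for process changes in those who adhered, so it matters who counts as adherent.

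**Working it through.** The plan gives no figure for the per-protocol set, so there is none to reproduce.

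**1. Attendance and the rule.** Inputs: 21 sessions, drop-out at 5 consecutive absences (Group Psychoeducation). With k sessions attended there are k + 1 gaps of at most 4 absences each, so avoiding the rule requires k + 4(k + 1) ≥ 21, that is k ≥ 17/5 = 3.4, hence k = 4. Example: sessions 5, 10, 15 and 20. Enumerating all 2^21 attendance patterns confirms 4 as the minimum, with 35 qualifying four-session patterns. 4/21 = 19%. Conversely, one five-session gap with all else attended gives 16/21 = 76% and is a drop-out.

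**2. Window in which a recurrence can trigger the rule.** Assume weekly sessions start at about randomisation. The protocol's administration of the group measures at weeks 3, 10 and 21 of follow-up suggests this. The last possible run of five absences is sessions 17 to 21, so the recurrence must fall in roughly weeks 0 to 16.

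**3. Share of patients at risk.** Inputs: 60% control and 38% psychoeducation recurrence (Sample size). Assumptions not in the document: these are 96-week figures, and the hazard is constant.
- Control: hazard = −ln(0.40)/96 = 0.00954 per week. By week 16: 1 − exp(−0.00954 × 16) = 14.2%. As a share of control events: 14.2/60 = 24%.
- Psychoeducation: 1 − 0.62^(16/96) = 7.7%.
- Range for controls: with the Background's figure of about 50% at one year instead, 1 − 0.50^(16/52) = 19%.
- On 179 per arm: 0.142 × 179 ≈ 25 controls and 0.077 × 179 ≈ 14 psychoeducation patients at risk.

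These are patients who relapse early enough. How many would then miss five sessions is not known.

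**4. Effect on the analysis if drop-outs are excluded.** Simulation with at least 200,000 patients per arm and exponential relapse times calibrated to 60% and 38% at 96 weeks. Assumptions not in the document: a share q of relapsers misses 8 weeks, and other absences occur at random at 25% per session. (The article's 25% refers to patients who may not attend, so this is only a working value.)

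| q control / psychoeducation | True rate ratio | Ratio after exclusion |
|---|---|---|
| 0.25 / 0.25 | 0.52 | 0.52 |
| 0.5 / 0.5 | 0.52 | 0.53 |
| 1 / 1 | 0.52 | 0.54 |
| equal, any of these | 1.00 | 1.00 |
| 0.25 / 0.5 | 1.00 | 0.94 |
| 0.5 / 0.25 | 1.00 | 1.06 to 1.07 |
| 0.25 / 0.75 | 1.00 | 0.87 |
| 0.75 / 0.25 | 1.00 | 1.14 |

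With q equal in both arms at 0.25, 0.5 and 1, 96-week relapse in the retained set falls from 60% to 58%, 57% and 53% (control), and from 38% to 36%, 35–36% and 32% (psychoeducation).

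**5. Effect of the proposed change.** In the same simulation only absences before a first recurrence were counted, and drop-outs were censored at the fifth missed session with earlier recurrences kept as events. The ratio then agreed with the intention-to-treat ratio to within about 0.001 in every scenario. This is partly by construction, because absences unrelated to relapse were random in the model.

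**The case against.** - **The rule may not be the whole definition.** The article states one drop-out criterion and does not say that everyone else is adherent. The full protocol or SAP may add a minimum attendance. This stands, so the absence of such a minimum is not held against the plan. What is criticised is the criterion that is stated, which an added minimum would not repair.
- **Analysed as a drop-out need not mean excluded.** It could mean censored at drop-out, and a recurrence that precedes the absences would then still count. This stands too. The distortion arises under exclusion, and the text does not rule exclusion out.
- **Nothing says that relapsed patients miss five sessions in a row.** Correct. The link is a plausible inference.
- **The comparison barely moves when absence is alike in both arms.** Correct under the assumptions above. The article describes arms matched on everything but content and delivery style. A reader might infer that the per-protocol comparison is biased as a matter of fact. The document does not support that: bias in the ratio needs a difference between arms in relapse-driven absence. What falls even with equal absence is the absolute relapse rate.
- **A reader might take all relapses in the 21 weeks as removable (about 18% of controls).** That is too many, because five sessions must still remain.
- **The 4-of-21 case is extreme.** Of 5,985 four-session patterns, 35 (0.6%) escape the rule. Absentees also receive the materials and a chance to discuss them, so attendance is not the same as exposure. The example shows what the rule permits, not what is likely.
- **The primary analysis is intention to treat.** This stands and limits the weight of the point.

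**Conclusion.** The point holds for a supporting analysis. The stated rule lets a primary event cause removal from the per-protocol set if drop-outs are excluded. On a constant hazard and 60% control recurrence at 96 weeks, about 14% of controls relapse early enough to be at risk (about 19% on the one-year figure in the Background). Either figure is an approximate upper bound on those removed for this reason.

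Under the simulation's assumptions, per-protocol relapse is understated by about 2 to 7 percentage points. The rate ratio hardly changes when relapse affects attendance equally, moves by about 6% with a two-fold difference between arms and by about 13–14% with a three-fold one, in either direction. The sizes depend on attendance assumptions that the document neither supports nor contradicts.

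The mismatch between the rule and exposure (4 of 21 can pass, 16 of 21 can fail) is exact arithmetic but secondary. A reader might infer that the trial's main result is compromised. It is not, because the intention-to-treat analysis does not use this rule.

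**What to change.** For the per-protocol analysis, in both arms:

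1. State that only absences before a first recurrence count towards drop-out.
2. In the time-to-event analysis, censor drop-outs at the date of drop-out (the fifth missed session, when the rule is met) and keep earlier recurrences as events, instead of excluding these patients.
3. Report the result as a descriptive, supporting analysis, and show the number of sessions attended by arm.

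This concerns the analysis only, not who may go on attending the groups. The cost is a few sentences and slightly more analysis work. The SCID-LIFE interviews already yield weekly scores from which a recurrence can be dated, but session-level attendance must be available to the analyst. One limitation remains: drop-out may be related to prognosis even before a recurrence, so censoring there may still be informative.

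Two other remedies are not recommended. A minimum number of sessions is a matter of preference, and early relapse would contaminate it in the same way. A simple complier-average causal effect analysis with randomisation as the instrument is not credible here: both arms are active, so a non-attender in one arm might have attended the other group.
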